## Abstract

**Introduction:**

Chronic inflammatory demyelinating polyneuropathy (CIDP) is one of the most common immune neuropathies leading to severe impairments in daily life. Current treatment options include intravenous immunoglobulins (IVIG), which are administered at intervals of 4–12 weeks. Determination of individual treatment intervals is challenging since existing clinical scores lack sensitivity to objectify small, partially fluctuating deficits in patients. End-of-dose phenomena described by patients, manifested by increased fatigue and worsening of (motor) symptoms, are currently difficult to detect. From a medical and socio-economic point of view, it is necessary to identify and validate new, more sensitive outcome measures for accurate mapping of disease progression and, thus, for interval finding. Digital health technologies such as wearables may be particularly useful for this purpose, as they record real-life data and consequently, in contrast to classic clinical 'snapshots’, can continuously depict the disease course.

**Methods:**

In this prospective, observational, non-interventional, single-center, investigator-initiated study, CIDP patients treated with IVIG will be continuously monitored over a period of 6 months. Clinical scores and blood analyses will be assessed and collected during three visits (V1, V2, V3). Additionally, activity, sleep, and cardiac parameters will be recorded over the entire period using a wearable device. Further, patients' subjective disease development and quality of life will be recorded at various visits (read-outs). The usability of the smartwatch will be assessed at the end of the study.

**Perspective:**

The study aims to evaluate different digital measurements obtained with the smartwatch and blood-based analyses for monitoring disease activity and progress in CIDP patients. In conjunction, both means of monitoring might offer detailed insights into behavioral and biological patterns associated with treatment-related fluctuations such as end-of-dose phenomena.

***Trial registration*:**

The study protocol was registered at ClinicalTrials.gov. Identifier: NCT05723848. Initially, the protocol was submitted prospectively on January 10, 2023. The trial was publicly released after formal improvements on February 13, 2023, after first patients were included according to the original protocol.

## Introduction

Chronic inflammatory demyelinating polyneuropathy (CIDP) is one of the most common immune neuropathies [11]. It is characterized by a progressive or relapsing disease course developing for more than 8 weeks, often leading to severe restriction of the patient's everyday life [5, 14]. Typical symptoms are symmetrical distal and proximal paresis, sensory disturbances, and reduced to absent reflexes. Therapeutic long-term options, in addition to glucocorticoids and plasma exchange, are mainly intravenous immunoglobulins (IVIG) (Van den [16], which must be administered repeatedly to ensure disease stability [9]. As typical intervals between IVIG applications range from 4 to 12 weeks, individual interval finding is sometimes difficult in the context of CIDP. In daily routine, treatment intervals primarily rely on clinical examinations, which frequently struggle to quantify patients' fluctuating deficits effectively. Alternatively, slight changes relevant to patients’ everyday lives are sometimes taken as indicators and lead to alterations of the individual dosing interval. Therefore, the subjective perspective of patients is even more relevant for the adjustment of the therapy intervals.

Moreover, some CIDP patients undergoing IVIG treatment often describe treatment-related fluctuations or an "end-of-dose" phenomenon at the end of their respective treatment cycle, which is characterized by increased fatigue and, eventually, deterioration of pre-existing neurological deficits [2, 3]. In addition, patients frequently report significant improvement shortly after the infusion, a phenomenon not yet explained from a pathophysiological standpoint. These gradual changes and fluctuations cannot be adequately reflected by current measurements, which only offer a ‘snapshot’ of the patient’s status at the time and place of examination [7]. Moreover, current outcome measures from prospective trials in IVIG treated patients do not allow meaningful conclusions for daily routine [1]. Consequently, dosing intervals today are usually based on insufficient information, as objectifiable parameters such as nerve conduction studies are neither dynamic nor sensitive enough to document the changing patient’s everyday limitations [2]. Since IVIG treatment must be critically reviewed from a medical and socio-economic point of view (availability, potential side effects, high costs) [4], new markers for disease activity are needed to monitor the patient’s status and optimize treatment continuously. Although there are initial attempts to more closely monitor the clinical development of patients [2], these require daily clinical measurements and are currently not routinely used.

Digital Health Technologies (DHTs), like connected wearables [6], provide nearly continuous real-life data collection with unparalleled frequency, allowing researchers and clinicians to transition from 'snapshot' assessments to more dynamic evaluations of patients' status [15]. As DHTs can increasingly document movement patterns, sleep behavior, and cognition, their use in neurology trials continues to grow [12]. Together with conventional measurements, this ‘digital phenotyping’ might lead to a more complete and continuous recording of deficits relevant to everyday life. Given the high need to better document fluctuating disability in CIDP patients, DHTs might both enable a better understanding of disease activity for individual patients and assist clinicians in drawing relevant therapeutic decisions for the individual CIDP patient in a precision-medicine-guided manner.

## Methods

### Aim of the trial

The goal of the EMDA CIDP study is to evaluate various widely available smartwatch-derived digital metrics and blood-based analyses for monitoring disease activity in CIDP patients treated with IVIG.

First, digital and blood-based measurements will be compared with subjective patient reports and established clinical scores. Second, exploratory analyses aim to understand longitudinal disease progression and its variability in individual patients. Thus, by monitoring a variety of digital and biological phenotypes of CIDP patients, individual determinants and measurements of disease activity patterns will be explored and characterized. Novel auspicious combinations of disease activity measurements may improve dose and interval optimization in the future. Considering the influence of behavioral traits such as physical activity and sleep on patients' metabolic state and various bodily functions [8, 10], we aim to explore the interplay between behavioral and biomedical characteristics in our patients. By monitoring both behavioral and biomedical parameters over time, we further aim to investigate the potential response of biomedical features to changes in activity or sleep patterns.

### Study description and study design

This prospective, observational, non-interventional, single-center, investigator-initiated study is being conducted at the University Hospital of Düsseldorf, Germany.

Upon introduction to the trial and written consent, CIDP patients treated with IVIG are enrolled in the study during the screening visit in conjunction with the baseline visit (V1). During this onsite visit participants are handed out a wearable (ScanWatch, Withings, Paris, France) and instructed in the use of the technology. After a 1-week period, a phone visit will be conducted to clarify any technical issues. Wearables are used to continuously record patients' activity, cardiac, and sleep parameters for a total of 6 months. In addition, a second onsite visit (V2) is scheduled after 3 months, and a final visit (V3) after 6 months. At all three onsite visits, clinical examinations, scores to classify CIDP-related symptom severity, and questionnaires regarding quality of life, quality of sleep, and the subjective occurrence of end-of-dose phenomena will be collected. In addition, a serum sample will be collected to analyze markers of neuroaxonal damage such as serum neurofilament light chain (sNfL). Furthermore, we aim to employ non-targeted proteomics to systematically analyze protein expression patterns in CIDP patient samples, aiming to identify potential biomarkers or therapeutic targets. By combining this comprehensive proteomic data with digitally captured behavioral information, we seek to uncover novel insights into proteomic-behavioral interactions in CIDP patients, ultimately improving disease understanding and facilitating personalized treatment strategies (see Fig. 1).

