**Fig. 1 Fig1:**
[figure not shown]
Graphical outline of the study protocol. *IVIG* intravenous immunoglobulins

Throughout the period, patients will receive their regularly scheduled IVIG infusions.

Sample size calculation: Given the exploratory and observational nature of our study, we do not have a specific hypothesis to test, making power analysis less suitable in this context where basic information on distributions is currently missing. The primary objective is to generate first-hand data to enable hypothesis formation and identify potential relationships for further examination in subsequent hypothesis-driven studies.

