### Arms and interventions

As this is an observational cohort study, there are neither interventions nor arms. Patients will be stratified by their biological and digital behavioral phenotypes retrospectively to assess differences in disease activity patterns.

It is planned to enroll approximately 60 patients in the study.

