### Eligibility criteria

CIDP patients treated with IVIG in constant intervals are included.

Further inclusion criteria are:Age ≥ 18 yearsProbable or definite CIDP patients according to the European Federation of Neurological Societies/Peripheral Nerve Society 2010 criteria [16].IVIG treated as follows:Documented evidence of objective response to IVIG, with clinically meaningful improvement. Clinically meaningful improvement is defined as one of the following: ≥ 1 point decrease in adjusted INCAT score, ≥ 4 points increase in I-RODS total score, ≥ 3 points increase in MRC Sum score, ≥ 8 kilopascal improvement in mean grip strength (one hand), or an equivalent improvement based on information documented in medical records and per the principal investigator's (PI) judgement.Must be on stable IVIG therapy, defined as no change greater than 10% in frequency or dose of immunoglobulin therapy or corticosteroids within 8 weeks prior to screening.Evidence of clinically meaningful deterioration on interruption or dose reduction of IVIG therapy within 24 months prior to screening, determined by clinical examination or medical records. Clinically meaningful deterioration is defined as one of the following: ≥ 1 point increase in adjusted INCAT score, decrease in I-RODS total score ≥ 4 points, decrease in MRC Sum score ≥ 3, mean grip strength worsening of ≥ 8 kilopascals (one hand), or an equivalent deterioration based on information from medical records and at the PI's judgement.

The exclusion criteria are:unable to use smartwatch or/ and smartphone device

To maximize recruitment potential in a rare disease and minimize bias in this real-world measurement cohort, other comorbidities are not considered causes for exclusions. While this might be a source of potential error, we assess patients at every visit for comorbidities or special life events to best correct for effects on intra-patient measurements.

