### Analysis strategy

The planned study is intended as an exploratory study, i.e. all results will be interpreted as hypotheses generating. We will correlate clinical, digital and proteomic parameters as well as markers of neuroaxonal damage at baseline and with regard to longitudinal changes. Exemplary analyses will include:Advanced machine learning algorithms, employing both linear and non-linear boosted regression, along with gradient boosted random forest trees and potentially other machine learning algorithms, will be implemented for integrative prediction and categorization of clinical parameters, using biomedical (inflammation markers, proteome, metabolome) data as the base.Data of the different digitally tracked features will be analyzed using time series analysis methods and will be screened for trends, autocorrelation and seasonality components as well as feature analysis and time series decomposition. Features and traits of this time series data will be correlated with clinical developments as well as with biological features such as promisingmarkers like sNfL or proteomic marker candidates.Aggregated digital measures of different timepoints in the treatment cycle will be compared repetitively with each other (e.g. first week after treatment vs. week before treatment) and screened for differences on an individual and a group level, which might point to end-of-dose phenomena. Further stratification might include subgroups based on clinical or biomedical features.Repetitive trends in digitally-acquired time series data will be analyzed and potentially modeled using time-split data, deploying autoregressive moving average models as well as other algorithms.

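### Infused immunoglobulin may surface as a disease marker, because the plan states no separation of drug-derived from patient-derived protein in the serum proteome

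*Protocol article*

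**What the plan says.** All references are to the protocol article; no SAP is at hand.

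- **Exposure.** Eligibility criteria: "CIDP patients treated with IVIG in constant intervals are included". Under Fig. 1: "Throughout the period, patients will receive their regularly scheduled IVIG infusions". Arms and interventions: "there are neither interventions nor arms". No study sample is planned off treatment.
- **Spread of regimens.** Introduction: "typical intervals between IVIG applications range from 4 to 12 weeks". The same section says that intervals depend mainly on clinical examination, with patients' own reports also playing a part.
- **Use of the proteome.** Study description and study design plans "non-targeted proteomics to systematically analyze protein expression patterns in CIDP patient samples, aiming to identify potential biomarkers or therapeutic targets". Analysis strategy plans machine-learning prediction and categorization of clinical parameters, "using biomedical (inflammation markers, proteome, metabolome) data as the base".
- **Sampling.** Serum is taken at V1 and at 3 and 6 months. No link to the day of infusion is stated.
- **Nearest safeguards.** Laboratory methods plans a depletion step before proteomics. Eligibility criteria requires therapy to have been stable over the 8 weeks before screening. Analysis strategy labels all results as hypothesis-generating, and aligns the digital measures, but not the blood measures, to the treatment cycle.

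**The concern.** Serum from a patient on IVIG contains the drug. A non-targeted screen cannot know which immunoglobulin peptides were infused and which the patient made. The amount of infused protein depends on dose, interval and time since the last infusion. If interval also depends on how the patient is doing, there is a path from disability to interval, from interval to circulating drug protein, and back to an apparent prediction of disability. A peptide on that path would say how the patient is currently treated, not how active the disease is.

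The stated long-term use is better dose and interval finding. A marker that restates the present interval cannot inform that choice. The same artefact could enter the planned stratification by biological phenotype and the planned search for links between proteome and behaviour, since infusion timing may affect both. It would also tend to recur in any later IVIG-treated cohort, where it could be mistaken for confirmation.

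**Working it through.** The plan has no figure to reproduce: about 60 patients are planned, expressly without a power calculation. The check is therefore a reading of the text plus illustrations on assumed inputs.

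**1. Is each link in the text?** Universal IVIG: yes. No comparator: yes. Proteome as screen and as model input: yes. Interval varying between patients and tied to clinical status: yes, in the Introduction. Dose tied to clinical status: not stated there. Infused protein excluded, flagged or adjusted for: not stated.

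**2. Where do the blood draws fall in the cycle?** Assume V1 is an infusion day and visits are at 13 and 26 weeks. Weeks since the last infusion is the remainder after dividing by the interval.

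| Interval (weeks) | 4 | 5 | 6 | 7 | 8 | 10 | 12 |
|---|---|---|---|---|---|---|---|
| V2 | 1 | 3 | 1 | 6 | 5 | 3 | 1 |
| V3 | 2 | 1 | 2 | 5 | 2 | 6 | 2 |

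At V2 the draws range from 8% (1/12) to 86% (6/7) of the cycle.

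**3. How far could total IgG differ by interval alone?** The documents give no dose. Assumptions, for illustration only: 0.4 or 1.0 g/kg per infusion, 70 kg, 45% intravascular, 3 L plasma, own IgG 10 g/L, half-life 3 or 4 weeks, one compartment at steady state.

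- Increment per infusion = dose × 70 × 0.45 / 3, so 4.2 g/L at 0.4 g/kg and 10.5 g/L at 1.0 g/kg.
- With r = 0.5^(interval/half-life), trough excess = increment × r/(1 − r).
- Half-life 3 weeks: r = 0.397 at 4 weeks and 0.0625 at 12 weeks. Half-life 4 weeks: r = 0.5 and 0.125.

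| Dose, half-life | Excess at 4 weeks (g/L) | Excess at 12 weeks (g/L) | Ratio of total IgG |
|---|---|---|---|
| 0.4 g/kg, 3 weeks | 2.76 | 0.28 | 12.76/10.28 = 1.24 |
| 0.4 g/kg, 4 weeks | 4.20 | 0.60 | 14.20/10.60 = 1.34 |
| 1.0 g/kg, 3 weeks | 6.91 | 0.70 | 16.91/10.70 = 1.58 |
| 1.0 g/kg, 4 weeks | 10.50 | 1.50 | 20.50/11.50 = 1.78 |

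This is undepleted serum. If the longer interval goes with the larger dose (0.4 g/kg at 4 weeks against 1.0 g/kg at 12 weeks), the ratio falls to 12.76/10.70 = 1.19 or 14.20/11.50 = 1.23.

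**4. Could a protein with no disease content be flagged?** Simulation: 60 patients, 2,000 runs, intervals spread evenly over 4 to 12 weeks, one dose size, assay noise SD 0.2 on the log scale, Pearson test at two-sided 0.05. The assumed correlation between severity and a shorter interval drives the result.

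- Correlation 0: about 5% flagged, the nominal rate. Giving IVIG to everyone does not by itself create an association.
- Correlation 0.3, own-protein background 0.5 of one dose's increment: 19–24% with random sampling and 36–39% at trough.
- Correlation 0.3, background matched to step 3 (10/10.5 = 0.95 to 10/4.2 = 2.4 increments): about 9–20% and 10–28%.

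Sampling at trough does not cure the problem, because interval still carries severity. Adjusting for the exogenous level brought the rate back to 3.9–5.3% in the runs with background 0.5. That used the exact level, which is known only in a simulation, so it shows the mechanism and does not validate particular covariates.

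**The case against.** **These are analysis-plan details.** Peptide filters and covariates usually sit in an SAP, and the article condenses a fuller protocol and calls its analyses exemplary. This has weight: the point may be settled in a document not shown. But the article itself names the proteome as a model input and aligns only the digital measures to the treatment cycle. Followed as written, it allows the artefact.

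**Samples are depleted.** A reader might infer that the models receive the unprocessed serum proteome. Laboratory methods does not support that. Depletion may shrink the effect, and the fold-differences above do not describe the depleted sample. What remains is that the article does not say which proteins are removed or mention infused immunoglobulin.

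**The link from status to regimen is loose.** The Introduction speaks of interval, not dose, and says that examinations often fail to quantify fluctuating deficits. A reader might infer that dose and interval are both set by clinical score; the text supports only a partial link for interval. No correlation is given, and with none there is no bias.

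**Therapy is stable.** Constant intervals limit change within a patient, so within-patient analyses are less exposed to regimen differences. They do not narrow the spread between patients.

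**Adjustment could destroy the target.** A reader might infer that every analyte must be adjusted for days since infusion. That would go too far. The study looks for end-of-dose patterns, which unfold along that very variable, and interval partly reflects severity. This objection stands and shapes the fix.

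**Conclusion.** The concern holds in a limited form. The plan as written lets infused immunoglobulin enter both the biomarker screen and the prediction models without a stated way to tell it from the patient's own protein. To the extent that interval follows clinical status, such peptides can be reported as disease markers.

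The size is unknown. The range of about 1.2- to 1.8-fold rests wholly on assumed dose, distribution, half-life and background, applies at the same dose and trough, and precedes depletion; 1.8 is its top, not its expected value. The false-flag rates depend equally on an assumed correlation and background.

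A reader might infer that the proteomic work is circular or useless. The documents do not support that: results are declared hypothesis-generating, longitudinal analyses are also planned, and the concern does not extend to the smartwatch recordings themselves. The exploratory label does limit how strongly a result is claimed, but it does not remove confounding by drug exposure. This is a worthwhile, inexpensive improvement to one stated aim.

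**What to change.** 1. Mark immunoglobulin heavy- and light-chain peptides before analysis. Keep them out of the main biomarker candidate set and the prediction models, and report them separately as a readout of exposure. State what the depletion step is expected to do to immunoglobulin.
2. For each blood draw, take infusion date, dose and interval from the treatment record. Compare the proteomic model with one using only dose, interval and days since infusion, and state for each candidate whether it adds to that benchmark.
3. For other proteins and for metabolites, show associations with and without these exposure variables as a sensitivity analysis, not as compulsory adjustment. Days since infusion also carries the end-of-dose signal, and interval partly reflects severity.

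**Cost.** Three data items per draw, a peptide filter and one additional model. No extra visit, no extra sample and no change to treatment. The downside is that a true signal in the patient's own immunoglobulins leaves the main screen, which matters in an immune neuropathy; it stays visible in the separate report.

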**Fig. 1 Fig1:**
[figure not shown]
Graphical outline of the study protocol. *IVIG* intravenous immunoglobulins

Throughout the period, patients will receive their regularly scheduled IVIG infusions.

Sample size calculation: Given the exploratory and observational nature of our study, we do not have a specific hypothesis to test, making power analysis less suitable in this context where basic information on distributions is currently missing. The primary objective is to generate first-hand data to enable hypothesis formation and identify potential relationships for further examination in subsequent hypothesis-driven studies.

### Arms and interventions

As this is an observational cohort study, there are neither interventions nor arms. Patients will be stratified by their biological and digital behavioral phenotypes retrospectively to assess differences in disease activity patterns.

It is planned to enroll approximately 60 patients in the study.

